## Methods

### Participants and Procedures

The sample size calculation was performed using the clustersampsi command [24] in Stata 12 (StataCorp LLC). The primary outcome measure is behavioral difficulties [25].

A minimum of 12 clusters (classes) of 10 students will be recruited. This is based on a mean effect size for universal classroom management programs of *d*=0.80 and an intraclass correlation coefficient (ICC) of 0.05 [26], a mean (standard deviation) in the intervention arm of 2.42 (2.05) indicating that behavioral difficulties are in the nonclinical range and a mean in the control arm of 5.13 (2.74) indicating that behavioral difficulties are in the clinical range [25], an average cluster size of 10 students and a coefficient of variation of cluster sizes of 0.42 [27], and a correlation between before-and-after measurements of 0.5. As the sample is being stratified by alternative provision versus mainstream school, 3 classes of each type per arm are being recruited across South East England.

All students aged 10 to 15 years in the schools taking part in the project will be eligible to participate. To ensure matched ages across the conditions, 5th grade students (aged 10 to 11 years) will be recruited from mainstream schools; the alternative provision schools have classes with mixed ages, and, therefore, students aged 10 to 15 years will be recruited from these schools. Students will be informed about the study by schools, which will disseminate information sheets and consent forms. Consent will be recorded in writing from parents with assent recorded from young people. Participants will be assigned a unique number and their data will only be identified by this number; consent forms and contact details will be stored securely and separately from anonymized study data. Participant lists of all classes and students will be obtained from schools.

An independent trials unit will randomize classes to management as usual or ReZone stratified by school type (alternative provision vs mainstream) using random sequence generation after classes have been recruited and baseline measures assessed. To reduce the predictability of randomization, classes will be randomized in blocks of 2, and allocation will be implemented via a secure online portal.

Management as usual was deemed an appropriate comparator as there is no routinely used mHealth intervention in classes when students feel overwhelmed. The trial will be open label.

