### Analytic Strategy

Data will be entered into an Excel (Microsoft Corp) spreadsheet by research assistants with a random 20% double-entered for cross-checking. Data will only be stored on the organization’s secured servers, accessible only by members of the research team. Data will be analyzed using Stata 12 (StataCorp LLC) in order to examine the effectiveness of ReZone in reducing emotional and behavioral difficulties and improving self-management, well-being, and health-related quality of life in young people in need of targeted support to engage with learning. Three models will be tested for each of the outcome variables with time nested within students within classrooms. In model 0, the null model without predictors will be computed to examine change in outcome (eg, behavioral difficulties) over time, and the ICC will be calculated. In model 1, the association patient-level grand mean centered age, ethnicity, and special educational needs will be entered as a level-1 predictor. In model 2, the condition (ReZone vs management as usual) will be entered. School-type (ie, alternative provision vs mainstream) will be entered as a fixed effect. The likelihood ratio test will be used to compare the fit of subsequent models. An intention-to-treat analysis will be performed with last-item carried forward imputation.

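### As listed, model 2 tests condition averaged over baseline and follow-up, which estimates half the follow-up difference; no condition-by-time term or baseline covariate is named

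*Protocol article*

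**What the plan says.** The Analytic Strategy section of the protocol article sets out the models one by one. The data structure comes first: "Three models will be tested for each of the outcome variables with time nested within students within classrooms". Scores are collected at baseline and 3 months later (Participants and Procedures), so each student contributes two response values.

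- Model 0 is a null model. It is said to have no predictors, and also to serve for looking at change in the outcome over time.
- Model 1 adds age, ethnicity and special educational needs.
- Model 2 adds the treatment: "In model 2, the condition (ReZone vs management as usual) will be entered".
- School type is a fixed effect, and successive models are compared by likelihood ratio test.

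Participants and Procedures says that classes are randomized after baseline measurement. The sample size there rests on d=0.80, "an intraclass correlation coefficient (ICC) of 0.05", "an average cluster size of 10 students and a coefficient of variation of cluster sizes of 0.42" and "a correlation between before-and-after measurements of 0.5". It also gives arm means and SDs of 2.42 (2.05) and 5.13 (2.74).

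**The concern.** Taken term by term, the only treatment parameter is a condition main effect in a model whose responses include the pre-randomization score. That parameter is the arm difference averaged over the two occasions. Randomization makes the baseline part zero in expectation, so the average is half the difference at follow-up. A likelihood ratio test of model 2 against model 1 tests that diluted quantity.

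The aim is to show that the app reduces difficulties. That calls for the difference at follow-up given baseline, or the difference in change, and no listed model contains either. The description of model 0 adds to the uncertainty: a model without a time term cannot show change over time.

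At stake are an effect reported at half its size and a substantial chance of missing a real effect of the planned size.

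**Working it through.** **Inputs** (Participants and Procedures): 12 classes of 10, hence 6 classes and 60 students per arm; ICC 0.05; CV of cluster size 0.42; r=0.5; d=0.80. The stated SDs give a pooled SD of √((2.05²+2.74²)/2)=2.42 (its match with the intervention mean of 2.42 is coincidence). The stated means then imply d=(5.13−2.42)/2.42=1.12. Alpha and target power are not stated; two-sided 0.05 is assumed.

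**The plan's own figure.** Design effect: 1+((0.42²+1)×10−1)×0.05=1.538. Classes per arm = 2(1.96+z)²/d² × 1.538/10, multiplied by 1−r²=0.75 if baseline adjustment is credited. For d=0.80:

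| Power | r ignored | r used |
|---|---|---|
| 80% | 3.77 → 4 | 2.83 → 3 |
| 90% | 5.05 → 6 | 3.79 → 4 |

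With d=1.12 the result is 2 to 3 per arm. Of these variants only d=0.80, 90% power and r ignored gives 6 per arm. The 12 classes therefore cannot be confirmed as resting on r=0.5.

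**Expected coefficient.** With a follow-up effect δ, complete data and equal weight on two occasions, the main effect has expectation (0+δ)/2=δ/2. A fixed effect for time does not alter this. In points, d=0.80 is 0.80×2.42=1.94 and would be estimated as 0.97; a difference of 2.71 would be estimated as about 1.36.

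**Standard error.** The mean of two occasions has variance factor (1+r)/2=0.75. Follow-up adjusted for baseline has 1−r²=0.75. Applying the same design effect to both gives SE=√(2/60×1.538×0.75)=0.196 SD units. With equal class sizes the design effect is 1+9×0.05=1.45 and the SE is 0.190. The SE is the same for both analyses and the signal is half.

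**Power, two-sided 0.05.** At d=0.80 the noncentrality is 0.80/0.196=4.08 with baseline adjustment and 0.40/0.196=2.04 for the main effect.

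| True d | Analysis | t (9-10 df) | z |
|---|---|---|---|
| 0.80 | Condition main effect | 45-47% | 53-56% |
| 0.80 | Baseline-adjusted | 95-96% | 98-99% |
| 1.12 | Condition main effect | 72-75% | 81-84% |
| 1.12 | Baseline-adjusted | >99% | >99% |

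Each range covers the two design effects.

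**Checks at d=0.80.**

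- Explicit variance components (class 0.05, student 0.45, residual 0.50) give a main-effect SE of √(2/6×(0.05+(0.45+0.25)/10))=0.200 and power of 52% (z) or 43% (t, 9 df). For condition-by-time the SE is √(2/6×2(1−0.5)/10)=0.183, with power 99% (z) or 97% (t).
- Varying r from 0.3 to 0.8 moves main-effect power only from 55% to 47% (z).
- A simulation of the likelihood ratio test itself, with unequal classes and school type as a fixed effect, gave a mean main-effect estimate of 0.40 and power of 57%. That test rejected in 8.7% of null trials, so 57% flatters it. The baseline-adjusted test gave a mean of 0.80 and 99%.

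**If condition-by-time is tested with only a class intercept.** Suppose class effects correlate 0.8 to 0.5 between occasions, which is an assumption because the protocol gives no value. The class variance of the change score is 2×0.05×(1−0.8)=0.02 to 2×0.05×(1−0.5)=0.05. The total change variance is 2(1−0.5)=1, so these are also its ICCs. The ignored design effect is 1.18 to 1.45 with equal classes (1.215 to 1.538 with CV 0.42). The type I error, 2(1−Φ(1.96/√design effect)), is about 7% to 11%.

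**The case against.** The strongest reply is that the text does not say condition enters solely as a main effect. Model 0 is meant to examine change, which only makes sense if time is in the model. On that reading it is an unconditional growth model with no substantive predictors, and entering condition could mean entering it as a predictor of change. The article is also condensed, and an analysis plan not shown may spell out the terms. This stands as far as intent goes: a reader might infer that the authors definitely planned a main-effect-only test, and the document does not prove that. It does not remove the point. The article lists the terms model by model, down to the centring of covariates, and the listed sequence followed literally misses the follow-up effect.

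A second reply is that only follow-up scores may be the response. Then a time level within students would have nothing to describe, and baseline would still be unused.

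A reader might also infer that the sample size depends on baseline adjustment because it cites a correlation of 0.5. The figures do not bear this out: the variants that use r give fewer than 12 classes. If r was used, it would suggest that the authors had a baseline-adjusted or change analysis in mind.

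**Conclusion.** The point holds for the models as listed: a condition main effect with baseline among the responses estimates half the follow-up difference, and model 0's stated purpose conflicts with its stated content. The halving follows from randomization after baseline and two equally weighted occasions with complete data; carrying baseline scores forward for missing follow-up would dilute the effect further.

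The power loss depends on the true effect. At d=0.80 power roughly halves, to about 45-55% from about 95-99%. It would be wrong to say that it halves in general: at the d of about 1.12 implied by the protocol's own means it is about 72-84% against over 99%, although the estimate is still halved. These figures rest on two-sided alpha 0.05, which the article does not state, on r=0.5, and on a t or normal reference in place of the planned likelihood ratio test.

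Because this concerns the primary comparison, the tested effect should be settled before results are interpreted.

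**What to change.** State the primary model as follow-up score regressed on condition, baseline score of the same measure, school type and the listed covariates, with a random intercept for class. Say that the condition coefficient is the treatment effect.

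If the repeated-measures form is kept, put time in the models, name condition-by-time as the tested effect, and allow a class-by-time random effect so that the test does not treat students' changes within a class as independent. In either case, correct the description of model 0 so that its content matches its purpose.

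The cost is a rewording of the Analytic Strategy. Both scores are already collected, so no new data are needed. The article says that protocol updates will be published; the update should be dated and should say whether it was made before outcome data were compared between arms.

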**Methods:**

The protocol is a cluster trial of 12 classes with N=120 students with classes randomized to ReZone or management as usual. Multilevel modeling will be used to compare ReZone versus management as usual accounting for classroom-level variation.

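### Condition is tested by an uncorrected likelihood ratio test on as few as 12 classes; at the planned ICC of 0.05 a nominal two-sided 5% test would reject a true null about 7–8% of the time

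*Protocol article*

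**What the plan says.** The Analytic Strategy section plans three nested models for each outcome, with "time nested within students within classrooms". The treatment comparison comes last: "In model 2, the condition (ReZone vs management as usual) will be entered". School type is also in the model: "School-type (ie, alternative provision vs mainstream) will be entered as a fixed effect". The models are compared as follows: "The likelihood ratio test will be used to compare the fit of subsequent models". No other test of condition is named, and neither a degrees-of-freedom method nor a small-sample correction is mentioned.

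On the number of classes, Participants and Procedures says: "A minimum of 12 clusters (classes) of 10 students will be recruited", with "3 classes of each type per arm are being recruited across South East England", which makes 6 classes per arm. The abstract agrees: "The protocol is a cluster trial of 12 classes with N=120 students with classes randomized to ReZone or management as usual". The sample size uses "an intraclass correlation coefficient (ICC) of 0.05".

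The article gives no significance level, sidedness or confidence level.

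**The concern.** Whole classes are randomized, so the evidence on condition lies in the differences between classes. After fitting an intercept, school type and condition to 12 classes, 12 − 3 = 9 class-level degrees of freedom remain.

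The chi-square reference for the likelihood ratio statistic fails here for two reasons. Maximum likelihood estimates the class variance without allowing for the fitted class-level terms, so the estimate is too small. The chi-square reference then treats that estimate as if it were known exactly. Both push the p-value down.

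The same comparison is planned for every outcome, including the primary one. The article says the trial will show whether the app is effective. A test that rejects a true null more often than its nominal level weakens that claim.

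**Working it through.** **Inputs from the article.** At least 12 classes, 6 per arm (3 per school type per arm); mean class size 10; coefficient of variation (CV) of class size 0.42; ICC 0.05; before-after correlation 0.5; d = 0.80. **Assumptions.** Two-sided 5% level, 80% power for the sample-size check, and any ICC other than 0.05.

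**1. Reproducing the planned size.**
- Individual randomization: 2 × (1.960 + 0.842)² / 0.80² = 24.5, so 25 per arm.
- Design effect: 1 + [(1 + 0.42²) × 10 − 1] × 0.05 = 1.538.
- Baseline adjustment: 1 − 0.5² = 0.75.
- 25 × 1.538 × 0.75 = 28.8 students, so 3 classes per arm. Two school types and two arms give 12 classes, as stated.

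**2. Exact check where class variance dominates and classes are equal in size.** The statistic is then 12 × ln(1 + t²/9), with t on 9 df.
- It exceeds 3.841 when t² > 9 × (e^(3.841/12) − 1) = 3.396, that is |t| > 1.843.
- The correct two-sided 5% cut-off on 9 df is 2.262.
- P(|t₉| > 1.843) = 9.8%. Without school type (10 df) it is 8.1%.

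**3. Simulation at realistic ICCs.** Data were generated with no treatment effect: 12 classes, 6 per arm, one value per student, and a random class intercept fitted by maximum likelihood. School type was in both models and the statistic was referred to chi-square on 1 df. The main settings used 15,000 replicates (Monte Carlo standard error about 0.2 points); other runs used 3,000 to 6,000. Ranges cover equal and unequal class sizes, with and without age, ethnicity and special-needs covariates where these were run.

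| Class ICC | Likelihood ratio test, false-positive rate |
|---|---|
| 0 (assumed) | 4.5–4.8% |
| 0.02 (assumed) | 5.2–6.5% |
| 0.05 (protocol) | 7.0–8.4% |
| 0.10 (assumed) | 8.3–10.3% |
| 0.20 (assumed) | 9.5–10.8% |

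At ICC 0.05 the 15,000-replicate results were 7.1% (equal classes), 7.7% (CV 0.42) and 8.1% (CV 0.42 with covariates). Leaving school type out gave 6.6%.

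**4. Two time points.** If the class effect is constant over time, a main effect of condition works on the student's two-time mean. Its variance is (1 + 0.5)/2 = 0.75 of a single measurement, so the relevant ICC is 0.05/0.75 = 0.067. The simulated rate there is 8.3–8.8%.

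**5. The replacement, under the same null.** A class-level t test on 9 df gave 4.4–5.4% over ICC 0.05–0.20. REML with a t reference on 9 df gave 3.4–5.7% over ICC 0.05–0.30. At ICC 0–0.02 the REML version is conservative (1.8–2.7%).

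**6. Power cost at d = 0.80 with 60 students per arm.** The standard error is √(2 × 1.538 × 0.75 / 60) = 0.196, so the effect is 0.80/0.196 = 4.08 standard errors. Power is 98.3% with a normal reference and 95.1% with a t reference on 9 df.

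**The case against.** **Level and intervals.** A reader might infer that the trial's declared 5% error rate and 95% intervals are broken. The article declares neither, nor does it say how an interval will be computed. What stands is conditional: p-values from this test are too small, and an interval would share the fault only if it came from the same large-sample fit.

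**Size.** A reader might also infer a fixed true error rate of up to 10%. The only ICC in the article is 0.05, which gives 7–8%. The upper figures need ICCs that are assumed here, and near-zero clustering removes the inflation. That limits the headline, but the protocol plans on 0.05 and so cannot rely on an ICC near zero.

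**Which effect is tested.** The figures hold for condition as a main effect, which is what the article describes. If a condition-by-time term were tested with only a random class intercept, the rate would be about 5% with no class-by-time variation. With change scores of ICC 0.05 it would be about 11%: P(|Z| > 1.96/√1.538).

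**Number of classes.** Twelve is a minimum, and more classes would reduce the problem. This is why 9 df should not be fixed in the text.

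**Left to the analysis plan?** Small-sample detail often is, and the literal wording is about comparing fit. But the article names the test itself, it is the only test of condition named, and nothing signals a correction. This objection does not remove the point.

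**Conclusion.** The concern holds in a limited form. The article fixes a large-sample test for a class-level effect with possibly only 12 classes. At the planned ICC the miscalibration is real and moderate: about 1.5 times an assumed 5% level. It approaches twice that level only at ICCs above the planned one. This rests on three assumptions: a two-sided 5% level, exactly 12 classes, and a main effect of condition with school type in the model. The documents do not support a claim that a stated error rate is violated or that the rate is 10% regardless of ICC.

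**What to change.** State that inference on condition will use a small-sample method, for every outcome:

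- adjusted class-level means or residuals compared by a t test with df = number of classes − 3 (9 if exactly 12 classes are recruited); or
- a REML fit with a small-sample t reference for condition, where the software supports it. The article names Stata 12, so availability there should be checked first. The class-level option needs only regression and a t test.

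Report that p-value with its t-based interval, and keep the likelihood ratio comparison as a description of model fit. State the significance level and sidedness in the same sentence.

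The cost is wording, settled before condition is tested, and a fall in nominal power from roughly 98% to 95% at d = 0.80 with baseline adjustment. Part of the higher figure comes from using a reference that is too lenient. The REML option is also somewhat conservative if the class ICC is close to zero.

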Research assistants will attend classes, and students will complete baseline paper questionnaires (this took place from February to April 2017). Classes will then begin management as usual or download and start using ReZone. Research assistants will attend classes to collect follow-up paper questionnaires 3 months later (this took place from April to June 2017).

A favorable opinion has been received from University College London (UCL) Research Ethics (number 7969/001), and the study is adhering to relevant ethical guidelines from the British Psychology Society [28]. The study is sponsored by UCL, and trial materials will be made available to the sponsor for auditing upon request. The trial is registered with ISRCTN [ISRCTN13425994], and the protocol is reported in line with Standard Protocol Items: Recommendations for Interventional Trials guidelines [29]. ReZone is reported according to guidelines for reporting mHealth interventions [30].

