## Discussion

The trial and its findings will develop an evidence-based mHealth self-management support intervention to help students engage with learning and manage their emotions. The findings will contribute to the growing use of technology to support children and young people with their mental health. Anticipated limitations of the proposed research include the fidelity of the intervention, assessed through teacher self-report and activity data; the content of management as usual, as different classes in this arm may use a variety of different social and emotional learning interventions despite not using ReZone, assessed through teacher self-report; and attrition, addressed by designing ReZone with young people to ensure it is usable and through using existing questionnaires that balance length with capturing the necessary range of relevant outcomes. Notwithstanding the above limitations, the proposed research will provide evidence as to whether ReZone is effective in helping young people to self-manage when feeling overwhelmed.

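### With a single follow-up, carry-forward gives each student lost to follow-up a change of zero, so dropout can shrink or distort the effect on change and understate its uncertainty

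*Protocol article*

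**What the plan says.** The missing-data rule is one sentence in the Analytic Strategy section: "An intention-to-treat analysis will be performed with last-item carried forward imputation". The article names no other method for missing data, and it gives neither a reason for this one nor a sensitivity analysis.

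The Participants and Procedures section describes one baseline questionnaire and one later assessment: "Research assistants will attend classes to collect follow-up paper questionnaires 3 months later". There is no intermediate visit.

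The planned model is longitudinal: "Three models will be tested for each of the outcome variables with time nested within students within classrooms". Condition is entered in the last of the three models. The article does not say whether the treatment effect is a condition-by-time term, a baseline-adjusted difference at follow-up, or a main effect of condition across both occasions.

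The Discussion lists among the expected limitations "attrition, addressed by designing ReZone with young people to ensure it is usable", together with the use of existing questionnaires of suitable length. No dropout rate is given for either arm.

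**The concern.** With two occasions, the only earlier value for a student who misses follow-up is baseline. Carrying it forward assumes that the student did not change at all, whatever the arm and whatever happened to classmates over the same term. The model then treats the copied score as a real measurement.

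Two things are at stake. The first is the size and possibly the direction of the estimated effect, which is what the primary aim of the trial asks for. The second is the stated precision: a copied score has no residual variation in change, so losing students can make the estimate look more precise than if nobody had been lost.

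The step is also avoidable. A longitudinal mixed model fitted by likelihood already keeps students who have only a baseline score, under the weaker assumption that data are missing at random.

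**Working it through.** **Inputs from the protocol article (Participants and Procedures).** 12 classes of 10 students, 6 classes per arm; effect 0.80 SD; ICC 0.05; before-after correlation 0.5.

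**Assumptions, because the document gives no figure.** Dropout of 10 to 30%, at random within arm; a general drift over the term of 0, 0.3 or 0.5 SD in either direction. There is no figure for dropout in the plan to reproduce.

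**Expected estimate.** Let d1 and d0 be the dropout shares under ReZone and control, t the drift common to both arms, and e the true effect on change (negative means fewer difficulties). Students who drop out contribute a change of 0, so the estimated difference in change is

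(1 - d1)(t + e) - (1 - d0)t.

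*Equal dropout d.* The drift cancels and the result is (1 - d)e:

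| Dropout in both arms | Calculation | Carry-forward estimate |
|---|---|---|
| 10% | 0.90 × -0.80 | -0.72 |
| 20% | 0.80 × -0.80 | -0.64 |
| 30% | 0.70 × -0.80 | -0.56 |

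*No true effect, unequal dropout.* With e = 0 the result is (d0 - d1)t. For t = -0.5:
- 30% under ReZone, 10% under control: (0.1 - 0.3) × -0.5 = +0.10 SD
- 10% under ReZone, 30% under control: (0.3 - 0.1) × -0.5 = -0.10 SD

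*True effect, unequal dropout, drift -0.3.*
- 30% against 10%: 0.7 × -1.1 - 0.9 × -0.3 = -0.77 + 0.27 = -0.50
- 10% against 30%: 0.9 × -1.1 - 0.7 × -0.3 = -0.99 + 0.21 = -0.78

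*No true effect, equal dropout.* (d0 - d1)t = 0, so there is no bias.

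**Precision.** This was simulated with the inputs above (8,000 runs, class-mean change scores compared by a t test on 10 degrees of freedom). At 20% equal dropout and a true effect of -0.80:

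| Analysis | Mean estimate | Mean SE | 95% interval coverage |
|---|---|---|---|
| Nobody missing | -0.80 | 0.214 | 94.9% |
| Observed data only | -0.80 | 0.234 | 95.0% |
| Carry-forward | -0.64 | 0.190 | 87.5% |

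The carry-forward SE is below the SE with complete data, so the interval is both off-centre and too narrow. A separate simulation gave SEs of 0.164 with carry-forward and 0.178 with nobody missing, and coverage of about 86%. The levels differ but the ordering is the same.

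In the scenario with no true effect, a drift of -0.5 SD and 30% against 10% dropout in either direction, the type I error was 7.6 to 7.7%. With no true effect and 20% dropout in both arms (drift -0.3 SD) it was 4.8%.

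**Dependence on how the effect is defined.** All the above treats the effect as a difference in change, or equivalently a baseline-adjusted difference at follow-up. If condition is entered only as a main effect across both occasions, the target is roughly the average of no difference at baseline and 0.80 at follow-up: (0 + 0.80)/2 = 0.40, even with nobody missing. Simulated under that reading (1,200 runs, sign dropped):

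| Equal dropout | Carry-forward | Observed data |
|---|---|---|
| 10% | 0.35 | 0.38 |
| 20% | 0.33 | 0.34 |
| 30% | 0.29 | 0.31 |

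A second check at 20% gave 0.32 and 0.33. Under that reading carry-forward adds only 0.01 to 0.03 to the shrinkage, and removing it restores little.

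**The case against.** Four objections deserve an answer.

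First, a reader might infer that carry-forward biases this trial's result whatever happens. The document does not support that. Without a true effect and with equal dropout there is no bias and the type I error stays near 5%. A false difference needs both unequal dropout and a general drift, and the article quantifies neither. Under equal dropout the point estimate errs toward no effect, and power hardly moves (about 85% with or without carry-forward at 20% dropout). This stands and limits the claim.

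Second, a reader might infer that deleting the sentence is enough because the mixed model is already planned. It is not: the shrinkage figures, and the benefit of using observed data, depend on a treatment effect defined as condition by time or as baseline-adjusted follow-up, which the article does not name. This stands and belongs in the fix.

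Third, the sentence speaks of an item, not an observation, and might concern only skipped answers in a returned questionnaire. Tied as it is to intention-to-treat with one follow-up, copying baseline is the likelier reading, but the wording needs clarifying. The item reading is no safer: a skipped question would take the answer to a different question, and students with no follow-up questionnaire would have no stated handling.

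Fourth, details of missing data may be left to an analysis plan. That does not apply here, because the article commits to a particular rule.

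**Conclusion.** The point holds in conditional form and should be fixed. The rule, naturally read, gives each student without follow-up a change of exactly zero and treats it as observed. For an effect on change, equal dropout of 10, 20 or 30% turns 0.80 SD into 0.72, 0.64 or 0.56. Dropout of 30% against 10% with a 0.5 SD drift yields a false difference of about 0.10 SD, whose sign depends on which arm loses more and which way scores drift. Intervals are too narrow, with coverage of about 86 to 88% at 20% dropout.

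The dropout shares and drifts are assumptions, dropout is taken as random within arm, and exact SEs and coverage depend on the model fitted. The actual distortion in this trial cannot be stated, and with little dropout it would be small. For that reason the point does not rank among faults that would invalidate the plan.

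**What to change.** Replace the carry-forward sentence by a primary analysis that includes all randomized students by the allocation of their class, in one of two ways:
- the likelihood-based mixed model on all observed scores, with the treatment effect stated explicitly as the condition-by-time term (or as the difference at follow-up adjusted for baseline); or
- multilevel multiple imputation that includes class, condition, school type, baseline score and the covariates.

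Add a sensitivity analysis for data not missing at random. Keep carry-forward at most as a labelled sensitivity analysis. Say separately how skipped items are handled, and do not fill one item from another.

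The cost is slightly more analysis work and somewhat wider, honest intervals (SE 0.234 instead of 0.190 in the 20% example). Follow-up ended in June 2017, before the article appeared, so the change must be dated, made before the data are analysed, and published as an update, as the Results section of the article commits to doing.
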